# Faecal incontinence intervention study (FINS): self-management booklet information with or without nurse support to improve continence in people with inflammatory bowel disease: study protocol for a randomized controlled trial

**DOI:** 10.1186/s13063-015-0962-0

**Published:** 2015-10-06

**Keywords:** Inflammatory bowel disease, Faecal incontinence, Nurse-led intervention

## Abstract

**Background:**

Inflammatory bowel disease, comprising Crohn’s disease and ulcerative colitis, is a life-long currently incurable illness. It causes bouts of acute intestinal inflammation, in an unpredictable relapsing-remitting course, with bloody diarrhoea and extreme urgency to access a toilet. Faecal incontinence is a devastating social and hygiene problem, impacting heavily on quality of life and ability to work and socialise. Faecal incontinence affects 2–10 % of adults in the general population. People with inflammatory bowel disease have a high risk of incontinence with up to 74 % affected. No previous study has explored conservative interventions for these patients.

**Methods:**

This randomised controlled trial will recruit 186 participants to answer the research question: does implementation of the UK nationally recommended guidance approach to stepwise management of faecal incontinence improve bowel control and quality of life in people with inflammatory bowel disease? We have worked with people with inflammatory bowel disease to translate this guidance into a condition-specific information booklet on managing incontinence. We will randomise participants to receive the booklet, or the booklet plus up to four 30-minute sessions with an inflammatory bowel disease specialist nurse. To be eligible, patients must be in disease remission and report incontinence. The primary outcome measure at 6 months after randomisation is the St Mark’s incontinence score. Other outcomes include quality of life, MY-MOP (generic tool: participants set two goals for intervention, grading goals at baseline and then re-scoring after intervention) and EQ-5D-5 L to enable calculation of quality-adjusted life years. Analysis will be on an intention-to-treat basis. Qualitative interviews will explore participant and health professionals’ views on the interventions.

**Discussion:**

Few high-quality studies of conservative interventions in inflammatory bowel disease, and none for faecal incontinence, have been conducted. We have collaborated with patients to design this study. Blinding to this behavioural intervention is not possible, but our self-report outcome measures with a degree of objectivity. There is genuine equipoise between the booklet only and booklet plus nurse arms, and the study will determine if additional support from a nurse is a crucial element in implementing advice.

**Trial registration:**

clinitrials.gov.uk: NCT02355834 (Date of registration: 12 December 2014).

Protocol version: 4.0. 08.04.15

**Electronic supplementary material:**

The online version of this article (doi:10.1186/s13063-015-0962-0) contains supplementary material, which is available to authorized users.

## Background

### Background and rationale

Inflammatory bowel disease (IBD, comprising mostly Crohn’s disease and ulcerative colitis) is a life-long currently incurable disease affecting approximately 250,000 adults in the UK, 2.2 million in Europe and 1.4 million in North America [1]. It causes bouts of acute intestinal inflammation in an unpredictable relapsing-remitting pattern, with bloody diarrhoea and extreme urgency to access a toilet. Chronic diarrhoea, rectal inflammation and reduced rectal capacity, disease or surgery which affect the continence mechanism, and a fatigable anal sphincter [2] all contribute to a high risk of faecal incontinence (FI) [3].

FI is a devastating social and hygiene problem, impacting heavily on quality of life and ability to work and socialise, and affecting 2–10 % of adults in the general population [4, 5]. Urgency and FI are accepted by both patients and clinicians in IBD flare-up, but at least a quarter of people with IBD also report extremely limiting symptoms persisting in remission [3]. Some young adults are completely housebound [6]. Interviews with people with IBD-related FI (IBD-FI) describe multiple life limitations: ‘*the fear of being faecally incontinent has a great impact on your life, and… this fear turns into stress and anxiety, which make it more likely that you will be incontinent… you enter a vicious cycle. It makes you nervous about going out, using public transport, going on holiday, and having intimate relationships*’ [6].

The imperative to find a toilet immediately is as limiting as frank incontinence and is reported as happening daily by 89 % of people with IBD during a disease flare and 66 % in remission [7]. Poor bowel control and the need for urgent toilet access are among the top ten concerns of people with IBD [8]. Some 81.3 % of people with IBD in the UK worry about the availability of toilets whenever they go somewhere new [7]. Crohn’s and Colitis UK (patient charity) have prioritised the issue of FI in IBD, funding studies on prevalence and quality of life [3], experiences of IBD-FI [6], help-seeking [9], and development of a patient-reported questionnaire for IBD-FI [10].

Previous work on FI in non-IBD populations has found that 70–80 % cure and improvement is feasible. Patients receiving conservative management in specialist nurse services are highly satisfied with their improvement and report improved ability to live with symptoms and better quality of life [11–13]. IBD nurse specialists are widespread in the UK National Health Service (NHS) [14], are highly valued by patients, and view FI as one of their core areas of practice [15]. However, our qualitative and quantitative work [3, 6, 9] has found that few IBD nurses offer any intervention specifically for FI. Reasons for this are unclear, but informal discussions suggest the primary barrier is lack of training for IBD nurses in managing FI. Small studies have suggested some benefit for individual specialist interventions for IBD-FI but no comprehensive approach has been evaluated.

The UK National Institute for Health and Clinical Excellence (NICE) [13] recommends a step-wise intervention algorithm for FI, starting with low-cost conservative interventions such as diet and anti-diarrhoeal medication, bowel retraining and pelvic floor exercises, estimating that 70 % of people with FI can be improved. There are several Cochrane reviews finding that treatments are effective for FI [12, 16, 17]. None has included people with IBD. Co-author AE has found that 18/27 (66 %) IBD patients managed in a nurse-led FI service reported improved continence and 63 % a significantly reduced continence score (unpublished audit). In 218 patients with radiation bowel disease (with similar symptoms) it was found that nurse intervention improves FI and quality of life and produces similar response to gastroenterologist intervention and is significantly better than a booklet alone, with improvements sustained at 1 year [18]. Our specialist clinical experience suggests that people with IBD are likely to respond well to the NICE algorithmic approach.

### Objectives

We aim to answer the research question “Does implementation of the UK nationally (NICE)-recommended approach [13] to stepwise management of FI improve bowel control and quality of life in people with IBD?” Our objectives are to determine the effectiveness of using IBD nurses to deliver the algorithm of care proposed by NICE for people with FI, compared to provision of the same information in a self-management booklet and to obtain detailed qualitative feedback from patients and staff on the best way of enabling health-seeking, the experience of the intervention and suggestions for future service development.

### Trial design

This is a two-arm parallel group randomised controlled trial (RCT) with 1:1 allocation intended to show superiority of IBD nurse intervention plus an information booklet, compared with an information booklet alone. The study has a total duration of 30 months.

## Methods

### Study setting

Six hospital centres with IBD clinics in metropolitan, urban and rural locations in England are recruiting and treating participants, in partnership with a Pragmatic Clinical Trials Unit (PCTU) in London. A list of sites can be obtained from the lead author.

### Eligibility criteria

The *Screening Case Report Form* (*CRF*) will be used to conduct pre-registration evaluation of participants for eligibility.

#### Inclusion criteria

Proof of IBD diagnosis (record of diagnostic endoscopy in patient notes).Between 18 and 80 years oldNo current flare-up of disease - stable disease and treatment status (in remission) for the past 3 months confirmed by documented normal results for inflammatory markers (C-reactive protein or faecal calprotectin [FCP]) recorded within a 3-month eligibility period; FCP tests to be repeated at recruitment to confirm IBD is in remission if no recent results documentedReporting FI at least once in the past year which is limiting self-reported quality of life and activities (determined by responses to survey above), enabling inclusion of the majority of people with IBD-FI whose quality of life is, in their own view, restricted

#### Exclusion criteria

Current disease flare-upCourse of specialist FI treatment in the past year (e.g. biofeedback, tibial nerve stimulation). From our previous work we hypothesise that this will be very few potential participants [4]Previous major anal fistula surgery or current perianal fistula (which can compromise anal sphincter function and control, increasing the risk of FI)Current stoma (faeces will be diverted)Current participation in another trialInability to give informed consent (for example, due to reduced mental capacity)Inability to read or speak sufficient English to understand study documents, procedures and requirements.

### Interventions

***Group 1*****(*****IBD nurse CONSULT + BOOKLET*****)**: will have 3–4 x 30-minute face-to-face sessions over 3 months with an IBD specialist nurse specifically focusing on bowel control. Participants completing at least three sessions will be considered to have completed the intervention. They will also be given the self-management booklet and access to all usual IBD care, including the routine local nurse-led IBD helpline.

#### Booklet development

We have worked with four people with IBD-FI to operationalise the UK NICE guidance on FI [13, 19] as a booklet for self-help for FI in IBD: *Managing Incontinence in Inflammatory Bowel Disease*. It includes practical advice on bowel habit, diet and fluids, anti-diarrhoeal medication, bowel retraining, pelvic floor exercises, practical coping and is based on our published advice for people with FI [20, 21] adapted to be IBD-specific.

#### Training IBD nurses

One or two IBD nurse specialists at each centre (maximum of 12 in total) will deliver the IBD nurse intervention. An intensive 1-day scripted training programme on managing FI will be delivered by two members of the study team. A checklist for intervention sessions included in the *Group 1 Intervention CRF* will monitor fidelity to the content and we will conduct two initial “test” sessions with each IBD nurse to gauge competence and 3–4 follow-up visits at random during patient consultations to gauge fidelity to the intervention.

***Group 2*****(*****BOOKLET alone*****)**: will receive the same booklet and access to usual IBD care as group 1. We recognise the potential influence on usual care of training the IBD nurses to deliver the intervention. We will emphasise during training the importance of trying not to influence usual care for the booklet arm participants and wherever feasible for another team member to see these patients in consultations (teams are large enough to accommodate this). In reality the IBD nurses are very busy managing acute aspects of IBD and are unlikely to have time to spontaneously provide more intensive input for FI. Our interviews (below) will explore perceptions of whether usual care was influenced by having the trial in progress.

### Withdrawal criteria

Participants have the right to withdraw from the study at any time, despite having given consent to take part, without having to give a reason for doing so. Their right and access to their usual NHS treatment will not be compromised in any way if they do withdraw. As indicated on the *Patient Consent Form* and explained in the *Patient Information Sheet*, all data collected before the point of withdrawal will be retained and analysed unless the patient specifically requests otherwise. We will ask those who withdraw if their withdrawal is due to the conditions of the study (i.e. too onerous/difficult to adhere to), seeking a simple yes/no answer. No further detail will be sought. This information will help to place any attrition in context and inform ongoing intervention design beyond this study.

### Strategies to improve adherence

No specific strategies will be employed. We will explore perceived adherence and ease of complying with the advice in the nested qualitative study (below).

### Relevant concomitant care

Participants will have full access to usual NHS care for IBD during the trial.

### Study outcome measures

Data will be collected by a self-completed booklet of questionnaires, given to the participant by a research nurse not conducting the intervention. Study outcome measures will be recorded at baseline and at 6 months after randomisation.

#### Primary outcome measure

• The St Mark’s faecal incontinence score [22] (0–24 scale) at 6 months after randomisation, compared between the study groups, analysed as a continuous variable. This is a widely used outcome measure in studies of FI and a 3-point difference in score has been found to be clinically relevant [23].

#### Secondary outcome measures

ICIQ–IBD (condition-specific questionnaire for symptoms and quality of life in IBD-FI) [10]Inflammatory bowel disease questionnaire [24] (the most widely used condition-specific IBD quality-of-life measure)Disease activity index to determine if disease activity level has changed (Harvey Bradshaw index for Crohn’s disease [25] and simple clinical colitis activity index for ulcerative colitis [26], and medical record of any escalation of treatment)MY-MOP [27] (generic tool: participants set two goals for intervention, grading goals at baseline and then re-scoring after intervention, giving an individualised profile of the most bothersome symptom, allowing analysis as a continuous variable)EQ-5D-5 L [28] to enable calculation of quality-adjusted life years (QALYS)Patient and NHS resource use for interventions (time and consumables used, time off work, travel costs)Study-specific tool: illness perceptions about FI and its treatabilityBrief illness perception score [29] to determine if illness perception influences completion and response to interventionStudy-specific tool: global perception of change, which interventions participants engaged in (e.g. diet change, pelvic floor exercises, use of anti-diarrhoeal medication) and ease of compliance with advice, satisfaction with intervention and qualitative comments, any IBD flare-up (definition: need to escalate or initiate medication/dose) during or since intervention. This will enable insights into which elements of the intervention are perceived by patients as most important.

A copy of trial outcome measures is available from the lead author on request.

### Participant timeline

The study flow chart is shown in Fig. 1.

**Fig. 1 Fig1:**
[figure not shown]
Patient flow diagram

### Sample size for the trial

Sample size is based on a published response (improvement) rate for conservative intervention for FI and a difference of 3 points in the St Mark’s FI score at 6 months being considered to be of clinical significance to people with FI but without IBD [23]. We will aim to randomise 186 people, with anticipated drop-out of 20 % (based on our previous intervention studies and clinical experience), which will be sufficient to detect a difference of 3 points on the St Mark’s scale assuming a standard deviation of 5, with a power of 90 %, using a 5 % significance level (74 needed per arm, increased to 93 to allow for drop-outs).

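### The sample size does not follow from its own inputs: 90 % power needs 59 to 60 evaluable per arm, not 74, and 74 per arm gives about 95 % power

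*Protocol article*

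**What the plan says.** The section Sample size for the trial (Protocol article, Methods) states that the planned number is "sufficient to detect a difference of 3 points on the St Mark’s scale". The SD is taken as 5, the target power as 90 % and the test level as 5 %. Drop-out is put at 20 %. The result is given in parentheses: "74 needed per arm, increased to 93 to allow for drop-outs". Twice 93 is 186, which agrees with the Abstract: "This randomised controlled trial will recruit 186 participants".

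The Trial design section describes a "two-arm parallel group randomised controlled trial (RCT) with 1:1 allocation intended to show superiority", and the primary outcome is analysed as a continuous variable. The calculation is therefore a comparison of two means with equal arms. Drop-out is the only inflation mentioned. The paragraph also opens by naming a published rate of improvement under conservative treatment as a basis for the size, but prints no such rate.

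**The concern.** The paragraph supplies everything needed to repeat the calculation, and its result is about a quarter too large. That is well beyond rounding or the choice between the normal and t formulas. The figure of 74 is also what one gets by allowing for 20 % loss on the correct answer, which suggests that the allowance was made once to reach 74 and again to reach 93.

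The paragraph fixes how many people are randomised and what the trial is said to be able to detect. If the 90 % target is the intended one, 36 to 38 more people are to be randomised than it requires. If 74 evaluable per arm is the intended figure, the stated power is wrong. Should follow-up fall short, a reader relying on this paragraph would conclude that fewer than 74 evaluable per arm loses the planned 90 %, when on the stated inputs 59 to 60 per arm retains it.

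**Working it through.** **Inputs.** From Sample size for the trial: difference 3, SD 5 (standardised difference 3/5 = 0.6), power 90 %, significance level 5 %, drop-out 20 %. From Trial design: two arms, 1:1, superiority. Assumption: two-sided test, because sidedness is not stated.

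**Attempt to reproduce 74.** Per arm, n = 2(z₁₋α/₂ + z₁₋β)² × SD²/difference².

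- Normal formula: 2 × (1.960 + 1.282)² × 25/9 = 58.4, rounded up to **59**.
- t-test (noncentral t): 59.35, rounded up to **60**.

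The stated 74 exceeds these by 74/59 = 1.25 or 74/60 = 1.23.

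**Other readings.**

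| Reading | Per arm |
|---|---|
| One-sided 5 %, 90 % power | 48 (normal), 49 (t) |
| Two-sided 5 %, 80 % power | 44 (normal), 45 (t) |
| Inflated for a rank test (efficiency 0.955, or 0.864 at worst) | about 62 to 70 |
| Two-sided 5 %, 95 % power | 73 (normal), 73.17 → **74** (t) |
| One-sided 1 %, 90 % power | 73 (normal), 74 (t) |

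The last two rows reach 74, but one contradicts the stated 90 % and the other the stated 5 %. Adjusting for the baseline score, as the Statistical methods section plans, lowers the requirement: by the factor 1 − r², an assumed correlation of 0.5 between baseline and follow-up gives 59 × 0.75 = 44.

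**Drop-out step.** 74/0.80 = 92.5, rounded up to 93, and 2 × 93 = 186. This step is correct in itself. But 59/0.80 = 73.75, which rounds up to 74. Dividing by 0.80 twice therefore gives exactly the printed sequence, 59 → 74 → 93.

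**Power at the stated sizes** (t-test, standardised difference 0.6, two-sided 5 %):

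| Evaluable per arm | Power |
|---|---|
| 59 | 89.8 % |
| 60 | 90.3 % |
| 74 | 95.2 % |
| 93 (no loss) | 98.3 % |

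The normal formula gives 95.4 % at 74 per arm.

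**What would make 74 right at 90 % power.** Either an SD of about 5.6 in place of 5, or a difference of about 2.7 points in place of 3.

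**What the stated inputs require after 20 % loss.** 59/0.80 → 74 or 60/0.80 = 75 randomised per arm, so 148 or 150 in total. The excess is 186 − 150 = 36 to 186 − 148 = 38 people, about 25 %.

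**The case against.** The strongest reply is that the discrepancy is on the safe side. The paragraph's main claim, that 186 people suffice for 90 % power, is true on its own inputs. Type I error, the primary estimate and the analysis model are untouched. This stands, and it limits the consequence: the trial is not underpowered. It does not make the statement that 74 are needed true.

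A second reply is that 74 may contain an allowance that the article omits, most plausibly for clustering by nurse. The Training IBD nurses section has at most 12 nurses delivering the intervention. Suppose clustering occurs in the nurse arm only and the inflation is averaged over both arms. With 6 nurses (74/6 = 12.3 participants each) and an assumed intraclass correlation of 0.04, the design effect is 1 + 11.3 × 0.04 = 1.45, averaging 1.23. With 12 nurses (6.2 each) and 0.10, it is 1 + 5.2 × 0.10 = 1.52, averaging 1.26. So the gap could be filled with unremarkable values. But the article states no such allowance, and it ties 74 directly to the 3 points, the SD and the 90 %. If an allowance exists, the paragraph has to name it.

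Third, the improvement rate may have been used in a calculation that is not printed. One can say only that it plays no part in the printed one. It is therefore safer to ask how it was used than to assume that it was not.

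Finally, two-sidedness is an assumption. This does not help, because a one-sided test moves the answer further from 74.

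**Conclusion.** The concern holds. Under the stated difference, SD, power and significance level, with a two-sided test and 1:1 allocation, 59 to 60 evaluable participants per arm are needed, not 74. At 74 the power is about 95 %. The paragraph as written is wrong either in the number it says is needed or in the power it states. A drop-out allowance made twice and a calculation at 95 % power both fit the printed figures, and the document does not decide between them. The consequence is a misreported basis for the trial's size, with 36 to 38 people beyond what the stated 90 % target requires, and not a loss of power.

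**What to change.** Retrieve the source calculation, then correct the paragraph in one of two ways:

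- **Keep 186.** State that 74 evaluable per arm gives about 95 % power for 3 points at SD 5, two-sided 5 %. If the margin was meant to cover something, such as clustering by nurse or a larger SD, say so and give the value used. Do not supply a reason afterwards that the original calculation did not contain.
- **Keep 90 % power.** State 59 to 60 evaluable per arm and 148 to 150 randomised in total.

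The first is the natural choice. It leaves the approved recruitment target alone and keeps a margin for an SD that is only assumed, and for a 3-point threshold that the paragraph says comes from people without IBD. In either case, state the sidedness of the test, and either show how the published improvement rate entered the calculation or remove the reference to it.

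The cost is one corrected paragraph, with no additional participants and no change to the design or analysis.

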### Recruitment

We will conduct an initial active case-finding phase comprising a survey of the prevalence of FI among patients attending routine IBD clinics at the six centres. We aim to include at least 2,000 people in this survey. Respondents to this survey, who indicate a willingness to participate in the trial, will be contacted by the research nurse. Potential participants will be screened for eligibility, in a telephone call. If eligible, patients will be sent the *Patient Information Sheet*, re-contacted and, if interested in participating, invited to attend an appointment with the research nurse to complete the *Informed Consent*, *Demographics and Randomisation CRF*, and the *Baseline Measures CRF*. Informed consent will be obtained.

Demographic characteristics of age, type of IBD, childbirth, history of perianal fistula and any related surgery, other colorectal surgery, and current disease activity and medications, will be recorded prior to randomisation. The patient will then be entered into the randomisation database and told whether they are in group 1 (nurse + booklet) or group 2 (booklet alone). Hospital consultants will be informed of the patient’s participation in the study via an entry made in the patient’s notes; the patient’s general practitioner will be informed via a letter.

